## Methods

### Study Design

This pilot study is a 12-week, parallel arm, randomized controlled trial. Participants will be randomized at a 1:1 ratio to a 12-week sleep education plus PHM device group or a sleep education alone comparison group at approximately 24 weeks gestation of pregnancy (Figure 1). This time period was chosen to capture data during the third trimester of pregnancy when sleep may worsen [1] while allowing sufficient time for study completion prior to birth. We will use blocked randomization to ensure equal group size due to the small pilot sample size. The study has been approved by the institutional review board of the University of Massachusetts Amherst. All participants will be required to provide informed written consent prior to enrollment.

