### Procedures

At the time of recruitment (t_0_) (14 to 24 weeks gestation), participants will complete a screening survey to determine their eligibility. At 24 weeks gestation (t_1_), eligible participants will enroll in the study and complete a baseline survey to assess demographic characteristics and secondary outcome measures. Both researchers and participants will be blinded to group assignment at the baseline assessment and during the educational intervention. All participants will receive an individual 30-minute educational intervention on sleep hygiene during pregnancy delivered by a study registered nurse at enrollment. The focus on the sleep education will be to provide tips on how to achieve a better night’s sleep during pregnancy such as managing pregnancy weight gain with aerobic activity and keeping a consistent schedule. Participants will also receive a sleep hygiene brochure, adapted from a Massachusetts Lung and Allergy sleep clinic sleep hygiene brochure to include information specific to pregnancy. We piloted the development of the brochure through an online survey that asked about the usefulness of the information and overall aesthetics. We used similar recruitment approaches (ie, Facebook) and eligibility criteria to identify women in the brochure development pilot as will be used for the pilot intervention to ensure the feedback is appropriate for the target population. Based on the participant feedback, we made modifications to the brochure’s graphical design; the information content was deemed useful. After completing the baseline survey and sleep hygiene education, participants and researchers will be unblinded to the group assignment (t_2_). Assignments will be made prior to the start of recruitment by randomizing study identification (ID) numbers into intervention or control group using Web-based randomization software [27]. The results of the randomization process will be placed into individually sealed envelopes labeled with study ID numbers. At t_2_, the study nurse will open the envelope for the ID number assigned to the participant and reveal group assignment. Those in the intervention group will then receive the intervention.

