### Data Analysis

We will use descriptive statistics to determine the feasibility and acceptability of the pilot intervention. Specifically, we describe recruitment and dropout rates in each group and noncompliance with the intervention among the intervention group only. To assess noncompliance we will use data from the IFTTT applet to determine the proportion of days the monitor was worn during the study period. High compliance will be defined as wearing the monitor at least 80% of days during the study period.

Qualitative methods will be used to determine the acceptability of the intervention, using a qualitative descriptive design [43,44]. The audio recorded interviews will be organized using NVivo 11 (QSR International Inc) software. Recordings will be professionally transcribed verbatim, and transcripts will be checked for accuracy. Descriptive coding will be used to identify and link comparable content and categorize data at a basic level [43]. For further analysis of descriptive codes, content analysis will be used to describe patterns and summarize findings in the data [44]. Memos will be written throughout the analytic process to capture the analysis process and the researchers’ responses to the data. Trustworthiness will be determined through peer debriefing between the research assistant and the principal investigator and the audit trial of documentation of the analysis, including coding, memos, and findings.

To examine the preliminary efficacy of the intervention, all secondary outcome variables will be modeled as continuous outcomes. We will compare baseline characteristics of the intervention groups to ensure randomization was successful. We will present the mean and standard deviation or median and interquartile range for each secondary outcome at baseline and postintervention. A paired *t* test will be used to compare baseline and postintervention means separately in each group. A Student *t* test will then compare the change in each measure between the two intervention groups. Finally, we will calculate within and between-group effect sizes using Cohen d (M_ΔI_ – M_ΔC_ / SD_pooled I and C;_ M_t2_ – M_t3_ / SD_pooled t2 and t3_).

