### Limitations

This study will, however, have important limitations that warrant discussion. First, the study requires that participants have access to mobile phones compatible with the study monitor; therefore, individuals of low socioeconomic status may potentially be excluded from the study [49]. However, lower income Americans have made gains in technology adoption including the use of mobile phones, which is likely to continue in the future. In addition, since there are multiple components of the intervention (ie, PHM and follow-up calls), we will not be able to discern which component explains differences between the groups, if any are observed. We will keep the follow-up calls briefs and use them primarily as a method of collecting information on the study’s feasibility throughout. However, we won’t be able to remove the potential effects repeated contacts can have on a participant’s ability to change behavior. Third, we will not exclude participants based on their use of any PHM. Therefore, control group participants may have access to a PHM during the study. However, none of the participants will be using our specific study monitor at baseline. Further, participants in the control group will receive study monitors at the end of the study to reduce attrition and limit the use of PHMs during the study. Last, due to the small sample size, we will not have sufficient power to detect any group differences in the secondary outcomes. Therefore, any significant or nonsignificant findings must be interpreted with caution. We will, however, be able to observed trends and generate hypotheses to be tested in a fully powered study.

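### Separate within-arm paired t tests are listed among the efficacy analyses, but change within an arm cannot isolate the device effect, so their p-values can mislead

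*Protocol article*

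**What the plan says.** The analysis block in Data Analysis opens with its purpose: "To examine the preliminary efficacy of the intervention, all secondary outcome variables will be modeled as continuous outcomes". Under that purpose it names a paired t test that "will be used to compare baseline and postintervention means separately in each group", then a Student t test: "test will then compare the change in each measure between the two intervention groups". Cohen d is to be calculated both within and between groups.

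Two other sections bear on what a within-arm change means. Study Design explains the 24-week start: "This time period was chosen to capture data during the third trimester of pregnancy when sleep may worsen". Procedures states: "All participants will receive an individual 30-minute educational intervention on sleep hygiene during pregnancy".

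Limitations adds that "due to the small sample size, we will not have sufficient power to detect any group differences in the secondary outcomes" and that "any significant or nonsignificant findings must be interpreted with caution". The sample size goal in Study Population is 10 women per group, with 12 per group to be recruited.

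**The concern.** The randomized question is what the device adds to sleep education. A paired t test in one arm asks something else: whether the score moved between baseline and 36 weeks for any reason. In the device arm, those reasons include the device, twelve weeks of advancing pregnancy, the education session and regression to the mean. In the control arm they are the same, without the device.

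The resulting p-values can be misread in two ways.

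- **Benefit hidden.** If sleep worsens over these weeks and the device fully prevents it, the device arm shows no change and its paired test has nothing to find.
- **Benefit suggested where there is none.** If both arms worsen equally, chance alone can make the control arm significant and the device arm not. That invites the reading that the device protected sleep, although the two arms were never compared.

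The article says the results will inform a grant application for a larger efficacy trial, so a misread signal would carry forward.

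**Working it through.** **Inputs from the protocol article.** The goal is 10 women per group, with 20% oversampling (Study Population): 10 × 1.2 = 12, which reproduces the stated 12 per group. Allocation is 1:1. The article gives no alpha, power figure or size of gestational change.

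**Assumptions.** Two-sided alpha is 0.05 for each test. The same true standardized change dz (mean change divided by SD of change) applies in both arms, so there is no device effect. The size of dz is unknown, so a range of 0 to 1.0 is shown.

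**Step 1: chance that one arm is significant.** With n per arm, the paired t statistic is noncentral t with n − 1 degrees of freedom and noncentrality dz × √n. Call the rejection probability p. At dz = 0, p = 0.05.

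**Step 2: chance that exactly one of two independent arms is significant.** This is 2p(1 − p). For example, at dz = 0.5 and n = 10: 2 × 0.293 × 0.707 = 0.414.

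| True change in both arms (dz) | p, n = 10 | Exactly one arm, n = 10 | p, n = 12 | Exactly one arm, n = 12 |
|---|---|---|---|---|
| 0 | 0.050 | 0.095 | 0.050 | 0.095 |
| 0.3 | 0.136 | 0.235 | 0.158 | 0.266 |
| 0.5 | 0.293 | 0.414 | 0.353 | 0.457 |
| 0.8 | 0.616 | 0.473 | 0.714 | 0.409 |
| 1.0 | 0.803 | 0.316 | 0.883 | 0.207 |

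By comparison, the planned between-arm t test is falsely significant in 5% of trials in every row, because a change shared by both arms cancels.

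**Step 3: how little the tempting pattern tells.** Take n = 10 and a control-arm worsening of dz = 0.5, and ask how often the control arm is significant while the device arm is not.

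- No device effect (device arm also changes by 0.5): 0.293 × 0.707 = 0.207.
- Full protection (device arm changes by 0): 0.293 × 0.95 = 0.278.

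The pattern appears in about 21% of trials with a useless device and 28% with a fully protective one.

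**Step 4: several outcomes.** The article names six scales, hence 12 within-arm tests. There are seven measures and 14 tests if PSQI sleep duration is analysed apart from PSQI quality. A simulation of 20,000 trials used seven measures, n = 10, dz = 0.5 in both arms for every measure, and correlation 0.3 to 0.7 between measures. At least one measure was significant in one arm only in 84% to 95% of trials. At least one between-arm test was falsely significant in 19% to 27%.

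**The case against.** The strongest reply is that the plan already contains the right comparison. The between-arm test of change, with its effect size, is valid under randomization. Nothing in the article says that significance in one arm only will count as efficacy. The outcomes are secondary in a feasibility pilot, and Limitations says that "any significant or nonsignificant findings must be interpreted with caution". All of that stands, and it limits the severity.

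It does not remove the point. The caution is tied to small sample size and power for group differences. A within-arm test fails to isolate the device effect at any sample size, and more participants would only make a shared change more reliably significant. The paired tests are also stated content under the efficacy aim, so they are not a detail left to an unseen analysis plan.

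A reader might go further than the document supports:

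- *Sleep is expected to worsen, and the study has no power.* Study Design says only that sleep may worsen. Limitations says power is not sufficient for group differences, which is not the same as none and does not refer to the within-arm tests.
- *The p-values will mislead.* With the between-arm test planned and caution stated, they can mislead; whether they do depends on the report.
- *The chance of a false positive over 21 tests is 66%.* That is 1 − 0.95^21 = 0.659, which treats the tests as independent. Each between-arm test uses the same change scores as two paired tests. Simulation with seven measures gives 58% when the measures are uncorrelated and 47% at correlation 0.5. These figures also assume no change over time in either arm. If scores really change, a significant paired test is a misattributed finding, not a false positive.
- *Any significant result must be a large overestimate.* At 10 per arm, between-arm significance needs |d| of at least 2.101 × √(2/10) = 0.94. Whether that overstates the truth depends on an unknown true effect. The 0.38 under Conceptual Framework is a pooled effect for healthy-eating and physical-activity interventions and is not a design assumption here.
- *The plan omits confidence intervals.* A condensed article commonly leaves that to the full plan, so it is not raised as a fault.

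**Conclusion.** The concern holds in a limited form. Paired t tests within each arm are assigned to preliminary efficacy, but they measure gestational change and the shared education together with any device effect. Depending on the size of the shared change, a single outcome is significant in exactly one arm in about 10% to 47% of trials with 10 per arm and no device effect. The probability is not monotone: it rises to 47% at dz = 0.8 and falls to 32% at 1.0, because both arms then tend to be significant.

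These figures rest on an assumed alpha of 0.05, normally distributed changes and an assumed range for the change, none of which the article gives. The logical point does not depend on them. The change is worth making, but it is modest in weight: the outcomes are secondary, a valid between-arm test is already planned, and caution is already advised.

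**What to change.** In Data Analysis:

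1. Remove the within-arm paired t tests from the efficacy analysis. Keep the planned means and SDs (or medians and interquartile ranges) by arm and time as description. If the within-group Cohen d is kept, label it descriptive as well.
2. Make the between-arm difference per outcome, adjusted for the baseline score already collected and shown with a 95% CI, the only efficacy comparison. The planned change-score test is valid; the adjustment is there to gain precision and to allow for chance baseline imbalance in a small sample.
3. State that within-arm change is not evidence of an intervention effect.

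The sponsor gives up 12 to 14 within-arm p-values, leaving 6 or 7 between-arm comparisons. Adjustment costs one degree of freedom per model (at 10 per arm, from 18 to 17). No new data are needed.

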At 36 weeks gestation (t_3_), all participants will complete an in-person follow-up survey to assess the same secondary outcome measures as at t_1_. Participants will also complete a brief qualitative interview to determine their satisfaction with the sleep hygiene education and, for those in the intervention group, the self-monitoring intervention. Participants will complete a final follow-up phone survey approximately 2 to 4 weeks after delivery (t_4_).

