### Covariates

We will collect information on demographic characteristics and eating habits. Demographic characteristics will include age, ethnic background, racial background, relationship status, level of education, employment status, hours worked per week, and income level. Eating habits will be measured using the Dietary Targets Monitor, a 9-item self-report questionnaire assessing consumption of fruits, vegetables, starchy foods, and other types of foods such as meat and fish [42]. Recommended standard portion for each group will be used to calculate daily, weekly, and monthly consumptions of different foods [42].

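### The between-arm efficacy comparison uses raw change scores (t test and Cohen d); it is valid, but adjusting for the baseline value already collected would usually be more precise and would remove the effect of chance imbalance

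*Protocol article*

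**What the plan says.** In the Data Analysis section of the protocol article, "all secondary outcome variables will be modeled as continuous outcomes". Paired t tests within each arm come first. Then a Student t test "will then compare the change in each measure between the two intervention groups". The between-group Cohen d has the difference between the two mean changes as its numerator.

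The baseline value of each outcome is available. Under Procedures, women at 24 weeks "complete a baseline survey to assess demographic characteristics and secondary outcome measures", and at 36 weeks "all participants will complete an in-person follow-up survey to assess the same secondary outcome measures as at t_1". Table 1 shows the same t1 and t3 pairing for all five outcome domains.

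On imbalance, the Data Analysis section offers one step: "We will compare baseline characteristics of the intervention groups to ensure randomization was successful". The Covariates section says "We will collect information on demographic characteristics and eating habits", but the Data Analysis section gives these variables no place in a model. Under Study Design, "We will use blocked randomization to ensure equal group size due to the small pilot sample size"; no stratification on baseline sleep is mentioned.

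**The concern.** Subtracting the baseline amounts to fixing the slope of t3 on t1 at 1. When the true slope is below 1, this over-corrects, and an arm that happens to start worse tends to look as if it improved more. With about 10 women per arm, sizeable chance differences at baseline are to be expected. Blocking balances the numbers per arm but not the baseline scores. Comparing baseline characteristics neither verifies the allocation nor removes an imbalance from the estimate.

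At stake is the quality of the preliminary efficacy estimates. Both the tested difference and the between-group Cohen d carry the same imbalance, and usually more noise than they need to. The article states this method outright, so it is not a detail left open for a separate analysis plan.

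**Working it through.** **Inputs from the protocol article.** 1:1 allocation (Study Design); target of 10 women per group, with 20% oversampling to 12 (Study Population); continuous outcomes measured at t1 and t3; unadjusted t test on change. The only related figure in the article reproduces: 10 x 1.2 = 12 per group. No power, SD or effect size is given for the secondary outcomes, so there is no efficacy calculation to reproduce.

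**Assumptions.** The correlation rho between t1 and t3 is not given, so a range is shown. The outcome SD is taken as equal at t1 and t3 and set to 1.

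**Step 1: expected imbalance.** With n = 10 per arm, the baseline difference D has SD sqrt(2/10) = 0.447. Its mean absolute value is 0.447 x sqrt(2/pi) = 0.36 SD.

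**Step 2: effect on the estimate.** Given D, the change-score estimate shifts by -(1-rho) x D. For D = 0.36 the size of the shift is:
- rho 0.3: 0.70 x 0.36 = 0.25 SD
- rho 0.5: 0.50 x 0.36 = 0.18 SD
- rho 0.7: 0.30 x 0.36 = 0.11 SD

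In simulation (100,000 trials per setting) the slope of the change-score estimate on D was -0.70, -0.50 and -0.31. For ANCOVA it was about 0.

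**Step 3: precision.** With N = 2n:
- Var(change) = 2(1-rho) x 2/n
- Var(ANCOVA) = (1-rho^2) x (2/n) x [1 + 1/(N-4)]
- Ratio = [(1+rho)/2] x [1 + 1/(N-4)]

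The last factor is the small-sample cost of estimating the slope. At 10 per arm it is 1 + 1/16 = 1.0625.

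| rho | (1+rho)/2 | x 1.0625 | Simulated ratio | SE, change | SE, ANCOVA |
|---|---|---|---|---|---|
| 0.3 | 0.65 | 0.69 | 0.70 | 0.53 | 0.44 |
| 0.5 | 0.75 | 0.80 | 0.80 | 0.45 | 0.40 |
| 0.7 | 0.85 | 0.90 | 0.90 | 0.35 | 0.33 |
| 0.8 | 0.90 | 0.96 | 0.96 | 0.28 | 0.28 |
| 0.9 | 0.95 | 1.01 | 1.02 | 0.20 | 0.20 |

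Break-even at 10 per arm: (1+rho)/2 = 16/17, so rho = 0.88. At 12 per arm, (1+rho)/2 = 20/21, so rho = 0.90.

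**Step 4: validity.** With no true effect, simulated type I error was about 5% for both methods at every rho.

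**Step 5: sensitivity to equal SDs.** Suppose the t3 SD is 1.3 times the t1 SD and rho = 0.7 (both assumed). The slope is 0.7 x 1.3 = 0.91. Var(change) is proportional to 1 + 1.69 - 2 x 0.91 = 0.87, and Var(ANCOVA) to 1.69 x (1 - 0.49) = 0.862. The ratio is 0.99, or 0.99 x 1.0625 = 1.05 after the small-sample cost. In that case ANCOVA gains no precision.

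**The case against.** The strongest reply is that nothing here is an error. A two-sample t test on change is a proper randomised comparison. These are secondary outcomes in a feasibility pilot whose Limitations section says that power is insufficient and that findings need caution. At rho 0.5 the 95% CI half-width falls only from about 0.94 SD (2.10 x 0.447) to about 0.84 SD (2.11 x 0.399), so neither analysis would settle a modest effect. Data collection has ended and assignment was revealed at t2, so a change of method now needs explaining. All of this stands and limits the weight of the point. It does not remove the gain: the estimates will still be reported, and the Results section says that the trial's results will inform a larger grant application.

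A reader might infer four stronger things that the article does not support:
- **That the planned test is biased or invalid.** It is neither; the dependence on imbalance is conditional on the baseline difference that happens to occur.
- **That ANCOVA is always more precise.** It is not when rho exceeds about 0.88, or when the t3 SD is clearly larger than the t1 SD.
- **That the next trial will be sized from this effect estimate.** The article does not say so. Its Discussion points mainly to recruitment, adherence, retention and implementation.
- **That a shift of 0.18 SD is to be judged against the pooled effect of 0.38 in the Conceptual Framework section.** That figure comes from healthy-eating and physical-activity interventions. It is not a planning value for this trial, in which both arms receive sleep education.

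Nor does the article say that baseline characteristics will be tested for significance. The stated purpose of the comparison is loosely worded, but no analysis decision hangs on it.

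**Conclusion.** The point holds as one of efficiency and conditional accuracy, not of validity. At about 10 per arm the mean absolute baseline imbalance of 0.36 SD moves the change-score estimate by roughly 0.11 to 0.25 SD for rho between 0.7 and 0.3, and the between-group Cohen d inherits the shift. Adjustment for t1 removes this dependence. Under equal SDs it also cuts the variance by about 30%, 20% and 10% at rho 0.3, 0.5 and 0.7, and by about 4% at 0.8. Rho and the SD ratio are assumptions throughout. Because the outcomes are unpowered and secondary, the benefit is better estimates, not a confirmatory conclusion. The change is worth making because it is nearly free.

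**What to change.** For each secondary outcome, replace the t test on change with a linear model of the t3 value on arm plus the t1 value of the same measure. Report the adjusted mean difference with its 95% CI. Base the between-group standardised effect size on that adjusted difference, for example divided by the pooled baseline SD; otherwise a change-based Cohen d would sit beside the adjusted estimate and still carry the imbalance. Present baseline characteristics descriptively, and drop the statement that they show whether randomisation succeeded.

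The cost is one degree of freedom per model, edits to the sentences on the test, the effect size and the baseline comparison, and no new data. Because data collection was completed in August 2018, the date of the change should be disclosed and the planned t test on change kept as a sensitivity analysis.

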### Study Population

We will recruit pregnant women who reside within approximately 50 miles of the University of Massachusetts Amherst campus. To be eligible to participate in the study, at the time of recruitment (t_0_) women must (1) be aged 18 years or older, (2) be 14 to <24 completed weeks gestation, (3) have no known maternal or fetal complications, (4) have a mobile phone compatible with the study PHM device, (5) have internet access, (6) be English speaking, and (7) be receiving prenatal care. We will exclude women with preexisting diabetes mellitus, hypertension, or a diagnosed sleep disorder, as some research demonstrated that associations between gestational diabetes and hypertension and a preexisting diagnosed sleep disorder would bias study results [28]. For the purpose of establishing feasibility and acceptability of recruitment and implementing the intervention, the sample size goal is 10 women per group. To account for attrition, we will oversample by 20%, recruiting 12 women per group.

Recruitment will be conducted through advertisements posted (1) at local commercial and community centers frequented by pregnant women in western MA, (2) at a women’s health clinic in western MA, (3) at community centers with diverse memberships such as churches, and (4) on Facebook and Craigslist. The study nurse will also recruit participants in person in the waiting room of the women’s health clinics at the University of Massachusetts Medical Center. During screening/enrollment, we will document the source of recruitment for each participant.

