## Results

Recruitment for this study began in September 2017 and ended in March 2018. Data collection for the primary and secondary aims was completed in August 2018. We anticipate that the data analysis for primary aims, evaluating the feasibility and acceptability of the intervention, will be completed by July 2019. We anticipate that the data analysis on the secondary aims, examining the preliminary efficacy of the trial on sleep quality and duration, sleep disturbance, excessive daytime sleepiness, fatigue, and depressive symptoms, will be completed by December 2019. The results from this trial will inform the development of a larger National Institutes of Health grant application to test the efficacy of an enhanced version of the sleep intervention that we plan to submit in the year 2020.

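### Minor improvement: with 10 to 12 women per arm, Hedges g with a 95% interval would serve better than plain Cohen d, mainly because of the interval

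*Protocol article*

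**What the plan says.** For the secondary outcomes, the Data Analysis section plans group summaries ("We will present the mean and standard deviation or median and interquartile range for each secondary outcome"), a paired t test within each arm and a Student t test on change between arms. It ends with the standardised effects: "Finally, we will calculate within and between-group effect sizes using Cohen d". Two formulas follow. The between-group one divides the difference in mean change by an SD pooled over the two arms. The within-group one divides the mean difference between two time points by an SD pooled over those time points. The article names no small-sample correction and no confidence interval.

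On numbers, Study Population states that "the sample size goal is 10 women per group" and adds: "To account for attrition, we will oversample by 20%, recruiting 12 women per group". Allocation is 1:1.

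On interpretation, Limitations concedes that "we will not have sufficient power to detect any group differences in the secondary outcomes" and that "any significant or nonsignificant findings must be interpreted with caution". On later use, Results says: "The results from this trial will inform the development of a larger National Institutes of Health grant application".

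**The concern.** Cohen d divides by an SD estimated from the sample. On few degrees of freedom, the expected value of one over that SD exceeds one over the true SD, so d is on average too far from zero whenever the true effect is not zero. The correction factor is known exactly and turns d into Hedges g. The article does not leave the estimator open: it names Cohen d and prints the formulas, so the choice can be reviewed as stated.

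The second aspect is precision. Because the plan concedes that its tests lack power, a reader looking for a signal is likely to turn to the standardised effects. A value of d given alone does not show how wide a range of true effects fits the data. Several scales are analysed this way (sleep quality and duration, sleep disturbance, sleepiness, fatigue and two depression scales), so some medium-looking values are likely by chance.

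**Working it through.** **Inputs from the article.** 10 women per arm (target) or 12 per arm (recruited); 1:1 allocation; Cohen d with a pooled SD.

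**Assumptions.** The between-group SD is that of the change scores, with normal data and equal variances. True effects of 0.2 to 0.8 are illustrative, because the article gives no expected effect, SD or significance level for this trial.

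**The plan's own figure.** Oversampling 10 by 20% gives 10 × 1.20 = 12 per arm, as stated. The article gives no effect-size, bias or power figure to reproduce.

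**Bias, between groups.** With m = 2n − 2 degrees of freedom, the exact factor is J(m) = Γ(m/2) / [√(m/2) Γ((m−1)/2)], and the relative overstatement is 1/J − 1.

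| n per arm | m | J | Overstatement | Bias at true d = 0.5 | Observed d = 0.50 becomes g |
|---|---|---|---|---|---|
| 10 | 18 | 0.9576 | 4.4% | 0.022 | 0.479 |
| 12 | 22 | 0.9655 | 3.6% | 0.018 | 0.483 |

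The usual approximation 1 − 3/(4m − 1) gives 0.9577 and 0.9655.

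**Bias against sampling error.** SE(d) ≈ √(2/n + d²/(4n)). At n = 10 and d = 0.5 this is √(0.2 + 0.00625) = 0.454, so the bias is 0.022/0.454, about 5% of one standard error. At n = 10 it is 0.009 (2% of one SE) for d = 0.2, 0.035 (8%) for d = 0.8, and zero when there is no effect.

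**Does the correction help?** Because g = J × d, its variance is J² times that of d: 0.9576² = 0.917, a cut of about 8%. Simulation at a true effect of 0.5 with 10 per arm gives a mean d of 0.523 and a mean g of 0.501, and the mean squared error falls by about 8%.

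**Bias, within groups.** With the SD pooled over two time points, the bias depends on the correlation between them, which the article does not give. Simulation at a true 0.50 with 10 women gives means of 0.524, 0.527 and 0.533 at assumed correlations of 0.3, 0.5 and 0.7, an overstatement of roughly 5% to 7%.

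**Precision.** The test statistic is t = d√(n/2). At d = 0.50 and n = 10, t = 0.5 × √5 = 1.118 on 18 df. Inverting the noncentral t gives noncentrality limits of -0.890 and 3.096. Dividing by √5 gives a 95% interval for the effect of -0.40 to 1.38. At 12 per arm it is -0.32 to 1.31.

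**Chance findings.** With no true effect, P(|d| ≥ 0.5) equals the two-sided tail of t beyond 1.118 on 18 df, which is 0.278. At 12 per arm, t = 0.5 × √6 = 1.225 on 22 df gives 0.234.

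**Illustration only.** n per arm = 2(1.96 + 0.8416)²/d² for 80% power at two-sided 5%. At 0.50 this is 62.8, so 63. At 0.479 it is 68.5, so 69. With 63 per arm and a true effect of 0.479, power would be 76.7%.

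**The case against.** The opposing case is strong on several counts.

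- **Absence in an article.** A condensed article commonly leaves a correction or an interval to the full protocol or analysis plan. This stands for the interval: its absence here is not an error. It has less force for the estimator, which the article names and writes out.
- **Size.** The bias is about 5% of one standard error at d = 0.5. This stands. Cohen d is a standard descriptive statistic and using it is not a mistake; g is simply a better choice at no cost.
- **Use in the larger trial.** A reader might infer that inflated effects will be carried into the sample size of the next study. The documents do not support that. Results says only that the findings will inform a grant application, for an enhanced version of the intervention, and the Discussion stresses recruitment, adherence, retention and implementation as what carries forward. The comparison of 63 with 69 per arm therefore rests on a use the article never states. Even under that use, an interval of -0.40 to 1.38 shows that the correction alone would not make the pilot estimate safe for planning.
- **False firmness.** A reader might also infer that the plan presents its effects as firmer than they are. Limitations declares low power and asks for caution, and d is to be reported beside group summaries and t tests. That answers the charge of concealment. The caution is general, though: it does not show, for any outcome, which effects remain compatible with the data.
- **Dependence on an unstated SD.** The 18-df figures assume the SD of change, and the formula does not say which SD is meant. This also stands. With equal variances at both times, the ratio of the SD of change to the raw SD is √(2(1 − ρ)), which is 1.18 at an assumed correlation of 0.3 and 0.77 at 0.7. That choice can move d by more than 4%.

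**Conclusion.** This is a minor, cost-free improvement and not a flaw in the design. Plain Cohen d at this sample size is biased away from zero by 4.4% (10 per arm) or 3.6% (12 per arm) between groups, provided the standardiser is the pooled SD of change. The within-group version is biased by roughly 5% to 7% at 10 women, under assumed correlations of 0.3 to 0.7. These amounts are small against sampling error. The more useful half of the recommendation is the interval, because at 10 per arm a d of 0.50 is compatible with effects from -0.40 to 1.38 and a value at least that large in absolute terms occurs by chance in about 28% of null comparisons. The point does not depend on any claim about how the larger trial will be sized.

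**What to change.** In the Data Analysis section, replace Cohen d with Hedges g and state that a 95% confidence interval will accompany each between-group effect. State in the same sentence that the standardiser is the pooled SD of the change scores, if that is what is intended, so that the degrees of freedom and the correction are defined. If within-group effects are kept, apply the correction and interval that match the SD pooled over time points, and label these effects descriptive. The cost is one or two lines of text and a standard function call. No new data, visits or participants are needed, and the reported effects become slightly smaller and openly imprecise.
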